### Statistical analysis

We will perform an exploratory data analysis on participants’ sociodemographic characteristics and to verify normality assumptions. Paired t-tests or Wilcoxon sign-rank tests will be used assess within-group changes, pre-to-post intervention, for all primary outcome measures. Independent t-tests or Mann Whitney-U tests will be used to assess between-group changes, pre-to-post intervention, for all primary outcome measures. We will use either a two-way repeated measures ANOVA or Kruskall-Wallis tests to determine changes over time for secondary outcome measures. For all tests, statistical significance will be set at *p* < 0.05.

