## Abstract

**Background:**

Neuromuscular electrical stimulation (NMES) is used to improve muscle strength clinically when rehabilitating various musculoskeletal disorders. However, the effects of NMES on muscle morphology and function in individuals with non-specific chronic low back pain (CLBP) have scarcely been investigated. Although research links deficits in the paraspinal musculature with subjective reports of pain and disability, it is unknown if treatment with NMES can help reverse these deficits. Therefore, the primary aim of this study is to compare the effects of two muscle therapy protocols with a medium-frequency electrotherapy device (the StimaWELL 120MTRS system) on multifidus muscle morphology and function in CLBP patients. The secondary aims are to determine the effects of these protocols subjective reports of pain intensity, pain interference, disability, and catastrophizing.

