**Methods:**

A total of 30 participants with non-specific CLBP, aged 18–60, will be recruited from local orthopedic clinics and databases. Participants will be randomized (1:1) to either the phasic or combined (phasic + tonic) muscle therapy protocols on the StimaWELL 120MTRS system. Participants will undergo 20 supervised electrotherapy treatments over a 10-week period. The primary outcomes will be multifidus morphology (e.g. cross-sectional area (CSA), fat infiltration) and function (e.g., contraction measured via %thickness change from a rested to contracted state, and stiffness at rest and during contraction). Secondary outcomes will include pain intensity, interference, disability, and catastrophizing. Both primary and secondary outcomes will be obtained at baseline and at 11-weeks; secondary outcomes measured via questionnaires will also be obtained at 6-weeks, while LBP intensity will be measured before and after each treatment. Paired t-tests will be used to assess within-group changes for all primary outcome measures. A two-way repeated-measures analysis of variance will be used to assess changes in secondary outcomes over time.

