In all but one of the studies cited above, researchers used traditional NMES protocols, in which the current is delivered at ranges of 10–100 Hz[24].This frequency range is sometimes described as being uncomfortable for patients, because skin impedance to current is thought to be inversely proportional to stimulation frequency[17, 18]. Medium-frequency electrical stimulation therapy, delivered at ranges of 1-10 kHz, is considered by advocates to penetrate the skin more easily than low-frequency stimulation. Proponents claim this makes it both more effective at muscle stimulation, and more comfortable for patients. Tolerance to treatment is critical because patients who tolerate higher current intensities experience greater real-time multifidus thickening[25, 26], which may lead to hypertrophic and strength gains over time. To date, the effects of medium-frequency electrical stimulation therapy on multifidus muscle morphology and function in CLBP have not been investigated. Therefore, the primary aim of this study is to investigate the effects of a 10-week muscle therapy intervention using the StimaWELL 120MTRS system (a medium-frequency electrotherapy device) on multifidus muscle morphology and function. Secondary aims are to investigate its effect on pain intensity, pain interference, pain catastrophizing, and disability.

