## Methods

### Study design

The proposed study is a two-arm randomized controlled trial with test–retest design. 30 participants will be recruited and randomized into one of two muscle therapy protocols for the lumbar spine: the ‘phasic’ group (*n* = 15) or the ‘combined’ group (*n* = 15) (Fig. 1).

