### Intervention

All research activities will take place at the PERFORM Centre, Concordia University. This center houses 8000m^2^ of laboratories, assessment suites, and lifestyle intervention spaces. It is equipped with the instruments needed to assess this study’s primary outcomes (MRI, Ultrasound), as well as space for conducting the intervention.

All participants will receive treatment with the StimaWELL 120MTRS system (schwa-medico, Germany) (Fig. 2). The StimaWELL 120MTRS system is a pre-modulated IFC (interferential current) electrotherapy device. It delivers current across up to 12 channels and offers preset pain and muscle therapy programs. The device also heats up to 40 °C.

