## Discussion

CLBP is a major health concern in Canada. It imposes a significant cost on our healthcare system and is detrimental to our population’s quality of life. Additionally, CLBP is linked to morphological and functional deficits in the multifidus muscle. To date, very little research has been done investigating the utility of electrotherapy in improving multifidus muscle thickness and CSA in CLBP patients. To the best of our knowledge, no research has been done into its effects on multifidus stiffness and fat infiltration in this population. This clinical trial constitutes novel research in two ways. First, it will help fill a gap in orthopedic NMES research, the majority of which has been focused on lower extremity use. Second, it will add to the body of research investigating the role of paraspinal morphology and function in CLBP. Moreover, if this treatment protocol is effective at improving multifidus morphology and function, our findings may lead to an improvement in the overall efficiency of CLBP treatments.

This study has several limitations. Firstly, our treatments are limited to twice per week. Many NMES protocols recommend treatments up to 6–7 times per week with portable units; unfortunately, this is not possible with the StimaWELL 120MTRS system. We have chosen to treat twice a week to maximize patient compliance, and an intervention period of 10 weeks was chosen to ensure an adequate number of exposures. Second, this study excludes individuals with a BMI > 30. We are taking this step because the presence of excessive adipose tissue and intramuscular fat can affect the validity of the shear-wave measurements, as fat attenuates the signal propagating from the ultrasound soundhead. We are also excluding individuals over 60 years old because intramuscular fat naturally increases with age, and this may confound our results. Therefore, the results of this trial may not be generalizable to adults over 60 years old, and those with a BMI > 30.

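### Within-arm and between-arm tests of the primary outcomes are planned without ranking, the Abstract names only the within-arm tests, and the sample size fits only those, although both arms receive active stimulation

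*Protocol article*

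**What the plan says.** The primary aim appears in two forms. In the Abstract (Background), "the primary aim of this study is to compare the effects of two muscle therapy protocols". At the end of the Background section, "the primary aim of this study is to investigate the effects of a 10-week muscle therapy intervention".

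The design has two randomised arms, phasic and combined, and neither is untreated or sham: "All participants will receive treatment with the StimaWELL 120MTRS system" (Intervention).

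The Statistical analysis section gives two families of tests for the same outcomes. First, "Paired t-tests or Wilcoxon sign-rank tests will be used assess within-group changes, pre-to-post intervention, for all primary outcome measures". In the next sentence, "Independent t-tests or Mann Whitney-U tests will be used to assess between-group changes, pre-to-post intervention, for all primary outcome measures". Nothing ranks them. For the primary outcomes the Abstract (Methods) carries over only the first: "Paired t-tests will be used to assess within-group changes for all primary outcome measures".

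The Sample size calculation section takes an effect size of 0.9 from earlier reports of improvement after NMES, with 0.05 and 80% power. It arrives at 12 per group, raised to 15 for drop-out, and does not say which test was sized.

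The Discussion looks ahead to the case that "if this treatment protocol is effective at improving multifidus morphology and function, our findings may lead to an improvement". Its limitations cover treatment frequency, BMI and age, but not the absence of a no-stimulation arm.

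**The concern.** The two aims are different questions. Comparing protocols needs the between-arm contrast, the only one that randomisation protects. Showing that the stimulation itself changes the muscle needs a comparator without stimulation, which this design does not have.

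A paired test within an arm answers neither. Change from baseline to 11 weeks contains any device effect together with natural course, repeat-measurement effects and the effect of co-interventions, which the protocol records but does not otherwise handle in the text shown. With the tests unranked and only the paired tests in the Abstract, the trial could be reported on significant pre-post changes. Two conclusions would then be within easy reach and unsupported: that the device works, and that one setting is better because its arm reached significance and the other did not.

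**Working it through.** **Inputs.** From the Sample size calculation section: effect size 0.9, level 0.05, power 80%, 12 per group before and 15 after the drop-out allowance. Assumptions: two-sided tests, and 0.9 read as a mean change (paired case) or a difference in mean change (two-sample case) divided by the SD of the change score. Going from 12 to 15 implies 1 − 12/15 = 20% drop-out; the rate is not stated.

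**1. Which test gives 12 per group?** Exact power from the noncentral t distribution.

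- Paired t-test within one arm: df = n − 1, noncentrality d√n. For n = 12: 0.9 × √12 = 3.118, critical t = 2.201, power 81.0%. For n = 11 power is 76.7%. So n = 12, the stated figure.
- Two-sample t-test on change: df = 2n − 2, noncentrality d√(n/2). For n = 20 power is 79.2%; for n = 21 it is 81.2%. So n = 21 per group.

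| Variant at d = 0.9, 80% power | n per group |
|---|---|
| Paired t, two-sided | **12** |
| Paired t, one-sided | 10 |
| Paired, normal approximation, two-sided / one-sided | 10 / 8 |
| Paired Wilcoxon (via asymptotic relative efficiency), two-sided | about 13 |
| Two-sample t, two-sided / one-sided | 21 / 16 |
| Two-sample, normal approximation, two-sided / one-sided | 20 / 16 |

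A repeated-measures interaction with f = 0.45 and an assumed correlation of 0.5 gives 12 in total, not per group. Of the variants tried, only the two-sided paired t-test yields 12 per group.

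**2. What does the planned size give the between-arm contrast?**

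- 12 per group: noncentrality 0.9 × √6 = 2.205, critical t = 2.074, power 56%.
- 15 per group: noncentrality 0.9 × √7.5 = 2.465, critical t = 2.048, power 66%.
- Difference detectable with 80% power: d ≈ 1.20 with 12 per group, d ≈ 1.06 with 15.
- If two active protocols differed by an assumed d = 0.5: power 22% (12 per group) or 26% (15 per group).
- To have 80% power at d = 0.9: 21 per group, or 21/0.80 = 26.25, so 27 per group with the implied drop-out.

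**3. Illustration: a device with no effect.** Suppose non-specific change alone is 0.3 to 0.5 SD of the change score (assumed values). With 15 per arm, the paired test is significant in 19% to 44% of arms. At least one of the two arms is significant with probability 1 − (1 − 0.1915)² = 35% to 1 − (1 − 0.4379)² = 68%, per outcome.

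**4. Illustration: comparing p-values between arms.** Suppose the true change is the same in both arms and w is the paired-test power. Exactly one arm is significant with probability 2w(1 − w).

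| d (same in both arms) | 12 per arm | 15 per arm |
|---|---|---|
| 0.9 (planned) | 2 × 0.810 × 0.190 = 31% | 2 × 0.899 × 0.101 = 18% |
| 0.5 (assumed) | 2 × 0.353 × 0.647 = 46% | 2 × 0.438 × 0.562 = 49% |
| 0.6 (assumed) | 2 × 0.475 × 0.525 = 50% | 2 × 0.580 × 0.420 = 49% |

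**The case against.** The strongest reply is that the comparison of protocols is already planned. The sentence after the paired tests prescribes independent t-tests or Mann-Whitney tests of change for every primary outcome, and a t-test on change is valid under randomisation. An abstract condenses, so its omission may be no more than shortening. This stands in part. A reader of the Abstract might infer that the plan has no between-arm analysis, or that the paired test is formally designated as primary. The documents support neither. What remains is that nothing ranks the tests, the Abstract pairs a comparative aim with tests that cannot address it, and the sample size fits only the within-arm test.

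A reader might also take the 18% to 50% in step 4 as false-positive rates of this plan. They are not. They apply only if someone infers an arm difference from discordant within-arm results, which no section prescribes.

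The Discussion sentence on effectiveness is conditional, so it is not a planned efficacy claim. The protocol asks about and records co-interventions; it does not say that they are permitted. The student doing the ultrasound is not blinded to allocation, but nothing is said about blinding to visit. Lack of blinding to allocation can also bias the between-arm contrast, so it does not single out the paired tests.

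**Conclusion.** The point holds in this form. The primary analysis is left open between a within-arm and a between-arm test, the two statements of the aim differ, and the Abstract and the sample size both lean to the test that does not use randomisation. With active stimulation in both arms, within-arm change can establish neither device effectiveness nor a difference between protocols, and no reanalysis of this two-arm design can establish the former.

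The firm number is the power. The stated 80% belongs to a paired test within one arm. The between-arm t-test has about 56% to 66% at d = 0.9 and reaches 80% only at d of about 1.20 (12 per group) to 1.06 (15 per group). This rests on two-sided testing and on reading 0.9 as a standardised effect on change. Baseline adjustment may raise the power somewhat, by an amount that the document gives no figures to calculate. Steps 3 and 4 illustrate what could go wrong and are not properties of the planned between-arm test, which avoids the step 4 error if it is made primary.

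**What to change.** - State one primary aim, phasic versus combined, in the same words in the Abstract and at the end of the Background section.
- In the Abstract (Methods) and in Statistical analysis, name the between-arm difference at 11 weeks, adjusted for baseline, as the primary analysis of the primary outcomes. The planned t-test on change is also valid; adjustment is preferred for efficiency.
- Report within-arm changes descriptively, as means with 95% confidence intervals and no significance claims.
- In the Discussion, limit conclusions to the comparison of protocols and list the absence of a no-stimulation arm as a limitation.
- In the Sample size calculation section, say that 12 per group was obtained for a within-arm paired test, and give the between-arm power (about 56% to 66% at d = 0.9) and the detectable difference (d of about 1.20 to 1.06).

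The cost in data and visits is nil, since these are wording changes. The cost in claims is real: the sponsor gives up any conclusion that the device is effective and declares a primary comparison below 80% power at the planned effect size. Restoring 80% at d = 0.9 would take 21 per group, or 27 with the implied 20% drop-out, against the 15 planned. If recruitment cannot be extended, the comparison should be presented as an estimate with its confidence interval.

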### Randomization

Participants will be randomized to treatment groups (1:1) using consecutively numbered sealed opaque envelopes (e.g., computer-generated randomization sequences) created by an individual not involved in the study.

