### Sample size calculation

While the effect of NMES on multifidus muscle morphology and function has not been thoroughly investigated in subjects with CLBP, previous reports showed significant improvements in multifidus thickness at rest and during contraction with medium to large effect sizes following a 6-week[19] and single NMES session[43], respectively. Based on these studies, we used a mean effect size of 0.9 to calculate our sample size at a level of confidence of 0.05 and 80% power. Accordingly, a sample size of 12 participants in each group was needed. We increased the sample size to 15 participants in each group to account for potential drop-out.

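### The between-arm test on unadjusted change scores is valid but usually less precise than baseline-adjusted ANCOVA; the gain depends on a correlation the protocol does not give

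*Protocol article*

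**What the plan says.** The Statistical analysis section sets two tests for the primary outcomes. Within arms, paired t-tests or Wilcoxon tests "will be used assess within-group changes, pre-to-post intervention, for all primary outcome measures". Between arms, "Independent t-tests or Mann Whitney-U tests will be used to assess between-group changes" from before to after the intervention, again for every primary outcome. Neither names a covariate.

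A baseline value exists for every primary outcome. The abstract says "Both primary and secondary outcomes will be obtained at baseline and at 11-weeks", and Table 1 marks both MRI and ultrasound at baseline and after the intervention.

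Allocation is simple: "Participants will be randomized to treatment groups (1:1") by sealed envelope, with no stratification on baseline muscle measures mentioned. The trial is small. The Sample size calculation section says "a sample size of 12 participants in each group was needed" and then "We increased the sample size to 15 participants in each group to account for potential drop-out".

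**The concern.** The abstract's primary aim is to compare two stimulation protocols, so the between-arm test is the randomised comparison. A change score is the follow-up value minus exactly one times the baseline. When the true slope on baseline is below 1, that subtraction over-corrects: people who start high tend to fall back, and part of any chance baseline difference between arms passes into the estimated difference in change. ANCOVA estimates the slope instead of fixing it.

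With 12 to 15 per arm, chance baseline differences are not small. Their SD, in units of the outcome's SD, is √(2/15) = 0.37 with 15 per arm and √(2/12) = 0.41 with 12. A difference above 0.5 SD in either direction then occurs in about 17% and 22% of trials. The change score carries (1 − r) times that difference into the result.

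At stake is precision: wider intervals and lower power than the same data could give. The test is named in the article, so this is a method already chosen and not a detail left to an unseen analysis plan.

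**Working it through.** **Inputs.** From the article: 15 per arm enrolled, 12 per arm after drop-out, effect size 0.9, level 0.05. Assumed: two-sided tests (sidedness is not stated), equal variance at baseline and 11 weeks, and a range for r, which the article does not give.

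**Step 1. The plan's own figure.** The article says "we used a mean effect size of 0.9 to calculate our sample size at a level of confidence of 0.05 and 80% power" and does not name the test. By the noncentral t:
- paired two-sided test, d = 0.9: n = 12 gives 81.0% power, n = 11 gives 76.7%. The stated 12 is reproduced.
- two-sample two-sided test, d = 0.9: 21 per arm (20 by the normal formula). One-sided: 16. The stated 12 is not reproduced.
- two-sample power at d = 0.9: 56% with 12 per arm, 66% with 15.

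The stated size therefore fits the within-arm test, and the between-arm comparison starts short of power. That is a separate matter, but it sets the background.

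**Step 2. Large-sample variance ratio.** With SD σ at both times:
- change score: Var = 2σ²(1 − r)
- ANCOVA residual: Var = σ²(1 − r²)
- ratio ANCOVA/change = (1 − r²) / [2(1 − r)] = (1 + r)/2

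**Step 3. Cost of estimating the slope.** On average ANCOVA's variance is inflated by 1 + 1/(N − 4): 1 + 1/26 = 1.038 at N=30 and 1 + 1/20 = 1.05 at N=24. Multiplying:

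| r | (1+r)/2 | N=30 | N=24 |
|---|---|---|---|
| 0.3 | 0.65 | 0.68 | 0.68 |
| 0.5 | 0.75 | 0.78 | 0.79 |
| 0.7 | 0.85 | 0.88 | 0.89 |
| 0.9 | 0.95 | 0.99 | 1.00 |
| 0.95 | 0.975 | 1.01 | 1.02 |
| 0.97 | 0.985 | 1.02 | 1.03 |

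The break-even value is r = 2/[1 + 1/(N − 4)] − 1, which is 0.926 at N=30 and 0.905 at N=24.

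**Step 4. Power if 0.9 is in raw-score SDs.** The standardised difference is 0.9/√[2(1 − r)] for the change score (N − 2 df) and 0.9/√(1 − r²) for ANCOVA (N − 3 df, slope cost included).

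| r | Change, 15/arm | ANCOVA, 15/arm | Change, 12/arm | ANCOVA, 12/arm |
|---|---|---|---|---|
| 0.3 | 52% | 69% | 43% | 58% |
| 0.5 | 66% | 77% | 56% | 66% |
| 0.7 | 87% | 90% | 78% | 82% |

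Without the slope cost, ANCOVA with 15 per arm would show 70/78/91%, so the cost is about one percentage point. At r = 0.9 on this scale both methods have power close to 100% and nothing is left to gain.

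**Step 5. Power if 0.9 is in change-score SDs.** The change-score test has 66% (15 per arm) or 56% (12 per arm) whatever r is. ANCOVA has 77% (66%) at r = 0.5, 72% (61%) at 0.7, 67% (56%) at 0.9 and 65% (55%) at 0.97, with the 12-per-arm figure in brackets. The gain is smaller on this scale at high r, and ANCOVA stays under 80% for r of 0.5 or more.

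**The case against.** A t-test on change is unbiased over randomisation and controls the type I error. The article states nothing false here and contradicts nothing, so this is a point about efficiency, on which trialists may reasonably differ. That stands, and it is why the point is a recommendation and not an error that must be corrected.

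Three stronger readings are tempting, and the article supports none of them.
- **That the plan throws the baseline away.** It does not. The baseline is subtracted, only with a slope that is fixed and not estimated.
- **That ANCOVA is free and always wins when r is below 1.** At this size it is not and does not. Step 3 shows a 4 to 5% cost and a break-even near 0.90 to 0.93. The article quotes a reliability of 0.97 to 0.99 for the CSA measurement. That is measurement reliability, not the 11-week correlation, but a high r for muscle size is plausible, and the gain there may be nil or slightly negative.
- **That regression to the mean is a further bias.** It can move a single trial's estimate, but over randomisation it is already part of the change score's variance. Counting it separately would count one defect twice.

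It is also tempting to say that the ultrasound measures gain most because they are noisier. The article gives no correlation for them, calls the techniques valid and reliable, and averages three repetitions. A lower r for percentage thickness change is plausible but undocumented.

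**Conclusion.** The point holds as a conditional gain in precision. The planned test is valid. ANCOVA is better for r up to about 0.90 to 0.93, with variance savings at N=30 of about 32%, 22%, 12% and 1% at r = 0.3, 0.5, 0.7 and 0.9. Above the break-even it loses about 1 to 3%. The case for changing rests on that asymmetry, since r is unknown and probably differs between outcomes.

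The figures assume equal variances at the two times and two-sided tests. The largest power gains also assume that 0.9 is measured in raw-score SDs, a scale that the article does not state. The direction of the result is firm; its size for any given outcome is not.

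**What to change.** In the Statistical analysis section, replace the between-arm t-test/Mann-Whitney sentence with wording such as: *For each primary outcome, the arms will be compared with a linear model of the 11-week value on arm and baseline value, and the adjusted difference reported with a 95% confidence interval. If residuals are clearly non-normal, the same model will be fitted on a log or rank scale, or a permutation p-value given.*

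Fix this before anyone sees outcome data by arm, so that the model is not chosen on the results.

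The cost is one sentence, one degree of freedom and about 4 to 5% of variance for estimating the slope. It needs no new data or visits. It does not replace a review of the sample size, which matches a paired test and not the comparison of two arms.

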### Secondary outcome measures

#### Pain intensity

Pain intensity will be measured with the Numerical Pain Rating Scale (NPRS). The NPRS measures pain intensity on a scale of 0—10, with 0 indicated no pain, and 10 indicating the worst pain imaginable. Changes of 2 or more points are clinically significant[40]. At baseline, midpoint, and endpoint, participants will be asked to rate the following using the NPRS: current low back pain, current leg pain, best and worst pain low back pain over the previous week, pain sitting and with movement over the past 24 h. Additionally, participants will be asked to rate their current low back pain prior to, and at the end of each treatment.

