### Possible effect modifiers

#### Catastrophizing

Pain catastrophizing will be assess using the Pain Catastrophizing Scale (PCS). The PCS is a 13-item questionnaire that assesses the participant's level of catastrophizing. Each item is rated from 0–4 for a possible total of 52. Higher scores indicate greater catastrophizing, with scores above 30 being clinically significant[42].

Participants will complete the BPI, ODI, and PCS at baseline, midpoint (6-weeks), and post-intervention (11-weeks).

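### Kruskal-Wallis is named as the rank alternative for secondary outcomes measured repeatedly on the same participants; it ignores the pairing, is conservative, loses power and has no group-by-time term

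*Protocol article*

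**What the plan says.** For the secondary outcomes, the Statistical analysis section of the protocol article offers two methods: "We will use either a two-way repeated measures ANOVA or Kruskall-Wallis tests to determine changes over time for secondary outcome measures". It comes after a check of normality assumptions, so the natural reading is that Kruskal-Wallis is used when normality is doubtful.

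The measurement schedule is the same for all these outcomes. Under Catastrophizing: "Participants will complete the BPI, ODI, and PCS at baseline, midpoint (6-weeks), and post-intervention (11-weeks". Under Pain intensity: "At baseline, midpoint, and endpoint, participants will be asked to rate the following using the NPRS". Table 1 marks the full NPRS, ODI, BPI and PCS at baseline, treatment 11 and the post-intervention visit.

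For the primary outcomes the same section names a paired rank test: "Paired t-tests or Wilcoxon sign-rank tests will be used assess within-group changes, pre-to-post intervention, for all primary outcome measures". It also names Mann-Whitney between arms. The abstract mentions only the repeated-measures ANOVA for the secondary outcomes.

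**The concern.** Three visits by one participant are not three independent groups. Kruskal-Wallis compares independent samples, so applied across visits it leaves the stable differences between people in the noise against which change is judged. A test that respects the pairing removes them.

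It is also a one-factor test. A two-way repeated-measures ANOVA gives a time effect and a group-by-time effect, and the second is the one that compares the two stimulation protocols. Kruskal-Wallis offers no counterpart to it.

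At stake are the patient-reported results on pain, interference, disability and catastrophizing. On the non-parametric branch, a moderate change could go undetected and the difference between arms in change over time would have no stated test.

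**Working it through.** **The plan's own figures.** The article gives no operating characteristic for this test, so there is no figure on this exact point to reproduce. Its sample size does reproduce: "we used a mean effect size of 0.9 to calculate our sample size", "at a level of confidence of 0.05 and 80% power". A paired two-sided t-test with a standardised effect of 0.9 needs 11.75, so 12 participants, which matches the stated 12 per group (15 with drop-out). The calculations below therefore use n = 15 for one arm and n = 30 for both arms pooled.

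**Inputs from the article.** Three visits per participant; two arms, 1:1; significance level 0.05 ("For all tests, statistical significance will be set at *p* < 0.05").

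**Assumptions, not in the article.** Normal scores with SD 1, equal correlation ρ between visits from 0.3 to 0.8 (0 shown for reference), and a linear fall of 0, d/2 and d over the three visits.

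**Statistics compared.**
- Kruskal-Wallis, visits as groups, N = 3n: H = 12/[N(N+1)] × Σ(R_j²/n) − 3(N+1), with ranks taken over all N values.
- Friedman, k = 3: Q = 12/[nk(k+1)] × ΣR_j² − 3n(k+1), with ranks taken within each participant.
- Both are compared with the 95% point of chi-square on 2 df, 5.99.

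**Why the level falls.** The difference between two visit means has variance 2(1−ρ)/n, but Kruskal-Wallis judges it as if the variance were 2/n. Under no change, H then behaves roughly like (1−ρ) times a chi-square on 2 df, so its type I error is about 0.05^(1/(1−ρ)):
- ρ = 0.3: 0.05^1.43 ≈ 1.4%
- ρ = 0.5: 0.05^2 = 0.25%

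This is a large-sample approximation. The simulation below gives slightly higher values at n = 15.

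**Simulation, 20,000 replicates per setting, % rejecting (Kruskal-Wallis / Friedman).**

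| Setting | ρ = 0 | 0.3 | 0.5 | 0.7 | 0.8 |
|---|---|---|---|---|---|
| No change, n = 15 | 4.7 / 4.5 | 1.8 / 4.8 | 0.6 / 4.7 | <0.1 / 4.7 | <0.1 / 4.8 |
| 0.5 SD, n = 15 | 19 / 15 | 13 / 20 | 9 / 27 | 6 / 41 | 4 / 58 |
| 0.5 SD, n = 30 | 36 / 30 | 31 / 40 | 26 / 54 | 21 / 76 | 18 / 91 |
| 0.9 SD, n = 15 | 53 / 41 | 50 / 55 | 49 / 71 | 48 / 90 | 48 / 98 |
| 0.9 SD, n = 30 | 85 / 75 | 88 / 89 | 91 / 97 | 94 / >99 | 96 / >99 |

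A repeat with fresh random numbers agrees to about one percentage point: type I error 1.7% at ρ = 0.3, and Friedman power for 0.5 SD of 21% to 57% (n = 15) and 40% to 90% (n = 30).

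**A fall of 0.8 SD.** At n = 15, Kruskal-Wallis against Friedman is 39% against 45% at ρ = 0.3 and 35% against 69% at ρ = 0.6. At n = 30, Kruskal-Wallis finds it 78% to 87% of the time over ρ = 0.3 to 0.8.

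**Group-by-time.** Let one arm of 15 fall by 0.9 SD and the other stay level. The group-by-time F test has power 56% (ρ = 0.5) and 80% (ρ = 0.7). Kruskal-Wallis across visits on the pooled arms rejects 15% and 10% of the time. If both arms fall equally, the F test rejects at about 5% and Kruskal-Wallis at 91% and 94%. Kruskal-Wallis responds to overall change and does not test whether the arms differ in change.

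**The case against.** The case for leaving it alone has several parts.

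- **Limited reach.** Primary outcomes have suitable paired and unpaired rank tests, and neither the primary analysis nor the sample size depends on this sentence. This stands, and it sets the severity.
- **Direction of error.** A reader might take a wrong test to mean false claims of benefit. The figures show the reverse: with positive correlation, the type I error is below 5%. The harm is lost sensitivity.
- **Size of the loss.** It is tempting to say that the test would miss real change, or that most of the power is lost. That is not generally so. The sentence does not restrict the analysis to within-arm change, and with both arms pooled a fall of 0.8 SD is usually found. At n = 15 and ρ = 0.3 the gap to Friedman is small, and at ρ = 0 there is no loss. Everything turns on a correlation the article does not give.
- **Comparator.** Repeated-measures ANOVA would give higher power still, but on normal data the plan would use ANOVA anyway. Friedman is the fair comparison, and even that is shown here only on normal data.
- **Use of the fallback.** One might infer that bounded scores in 15 per arm will usually fail a normality check. The article states no rule. As an illustration, for an assumed 0 to 10 rounded score with SD 2 and n = 15, a Shapiro-Wilk test rejects about 12% to 15% of the time for means of 3 to 5, and 42% for a mean of 2. Use for some outcomes is plausible; likely use in general is not shown.
- **A charitable reading.** Kruskal-Wallis could be meant as a comparison of arms. With two arms it reduces to Mann-Whitney, which the section already names separately, and the sentence is about change over time. This does not rescue it.
- **An unseen analysis plan.** The point is not an omission that another document might fill, because the article names a specific test that does not fit the data.

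**Conclusion.** The concern holds in limited form. As written, the rank alternative for secondary outcomes is a test for independent groups applied to repeated visits, and it cannot examine group-by-time. No other section repairs this.

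The consequence is a conservative test with reduced power. The loss is marked for moderate changes of about 0.5 SD and grows with within-person correlation: as ρ rises, Friedman gains power while Kruskal-Wallis loses it. It is modest at low correlation, and for large changes in pooled arms Kruskal-Wallis still usually detects the change.

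These sizes rest on an assumed correlation of 0.3 to 0.8, equal between visits, on normal scores with a linear trend, and on whether arms are analysed separately or pooled. The mismatch between test and design does not rest on any of them. This is a should-fix. The documents do not support calling it a threat to the trial's main conclusions.

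**What to change.** In the Statistical analysis section, replace Kruskal-Wallis for secondary outcomes with:

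- the Friedman test for change over the three visits, with Wilcoxon signed-rank for pairs of visits; and
- Mann-Whitney on change from baseline for the comparison between arms.

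The second item is needed because Friedman has no group-by-time term either. The sentence should also say whether change over time is tested within each arm or with arms pooled.

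A mixed model with group, visit and group-by-visit is an optional alternative and not part of the correction.

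The cost is one sentence, with no extra data, visits or participants. It should be settled before the outcome data are analysed.
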